#### Attention control

Participants will participate in passive stretching that we have previously tested [48, 49] and that are matched to session durations for cycling and exergame groups. Light intensity (RPE ≤ 9 or HRR ≤ 30%) stretching exercises include seated movements and static stretches that induce no changes in aerobic fitness.

#### Treatment fidelity

This study was designed to ensure treatment fidelity based on the NIH Behavior Change Consortium recommendations [50] and our experiences [48, 49]. The investigators and the study coordinator will oversee adherence to the protocol by all staff through review focused on screening compliance, study outcomes, intervention compliance (i.e., percent of exercise sessions attended, percentage of session duration in target intensity range, and exercise dose), and adverse events. Investigators and the study coordinator will ensure data creation and completeness through quality check and audits. Weekly meetings will be held among the investigators and study staff to ensure compliance to study protocol, while monthly fidelity checks will be performed (total 3% of intervention sessions) by the investigators to ensure accurate implementation of intervention protocols by using a previously used Fidelity Checklist [48]. Staff will be retrained as needed. The investigators will review 3% of session case forms (i.e., exercise logs) to assess for protocol drift and completeness.

#### Safety, retention, adherence, and validation

We have built in many strategies that have been successfully utilized in our preliminary studies to protect participants against risks, including ongoing monitoring of health status changes, appropriate equipment and personnel training, individualized prescriptions and supervised delivery for cycling and exergames training, and careful screening and informed consent. Interventionists will be fully trained using the Study Manual of Operations and will be able to consult with the investigators on an immediate, as-needed basis as well as at weekly meetings. During the course of the intervention, if a participant develops a contraindication to exercise, interventions will be terminated until the participant is re-cleared to resume exercise by their primary care provider or cardiologist.

### Data management

#### Data entry, coding, and storage

All participant data will be identified by a screening identification (ID) and a study ID for enrolled participants. Access to the links between name and IDs will be restricted to the study coordinator and interventionists involved in screening. Data collection forms returned to the research office by the study staff will be reviewed by the study coordinator for accuracy and completeness before entry into the study REDCap database [51, 52]. Data collection forms will then be stored in a specific office that is further locked and contains a lockable storage cabinet specific for data collection storage. Cognitive data from the NIH Toolbox Cognitive Battery will be exported from study iPAD into a university email account and then subsequently uploaded into REDCap by data collectors. Additionally, the study coordinator will verify data accuracy and completeness in REDCap. Any missing data will be assigned to a data collector for collection. If a participant withdraws from the study, all attempts will be made to collect data to allow for inclusion in the analysis. Reasons for withdrawal will be recorded. Data audits of electronic outcome data will be conducted by the study coordinator. If any discrepancies in scoring between the study staff who collected data and the study staff who entered data, a meeting with the investigators or study coordinator and involved study staff will be undertaken to ensure the correct data is in REDCap.

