### Study procedure

#### Study preparation and randomization

All staff will be adequately trained to ensure participant safety, blinding, data quality, and protocol adherence based on the Study Manual of Operations. Prior to any recruitment, the statistician will create a randomization schedule in Research Electronic Data Capture (REDCap). Qualified participants will be randomized after completing baseline data collection. The study coordinator will log into the REDCap randomization module and enter a participant’s name/age. The randomization module will assign the participant to a group and record the assignment in a database that is only accessible to unblinded staff.

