## Discussion

Developing interventions, with strong potential to prevent or delay the onset of AD in persons with SCD is critical. Aerobic exercise and cognitive training represent two promising interventions; however, their synergistic effects on preventing AD have not been evaluated. Our study will develop a novel, apple-TV, and iPad-based cognitive training that is immersive, naturalistic, and similar in tasks to real life, and therefore increases the ecologic validity of the treatment [29]. It is cognitively challenging but also increases exercise enjoyment.

All attempts have been undertaken to ensure the highest quality of study design and delivery of the Exergames Study. First, RCTs are considered the gold standard design for determining the causal effect of an intervention on an outcome. Alternatively, intervention trials commonly employ usual care or waitlist control groups or cross-over design. Usual-care or waitlist controls preclude assessing the Hawthorne or placebo effect of exergames, while cross-over designs are ideal for interventions without carry-over effects, which is also not the case for exergames. In addition, we have built in four strategies to prevent unblinding, another potential problem occurring in RCTs. The four unblinding prevention strategies include (1) assessors will not interact with other staff who are not blinded (i.e., exercise interventionists) and will participate in separate meetings, (2) investigators will be blinded to group assignments, (3) participants will be blinded to the study aims and reminded as needed not to discuss their experiences with the outcome assessor, and (4) randomization will be completed using permuted blocks. Additionally, age is a known, strong factor affecting cognition. While our aims are not focused on age, we will stratify enrollment by age to equalize age distribution across groups [55, 56].

In summary, the Exergames Study will be the first RCT to examine the additive/synergistic effects of a novel simultaneous moderate intensity, supervised aerobic exercise + cognitive training intervention on cognition and aerobic fitness. This study looks to advance AD prevention research by providing precise immediate and long-term effect-size estimates of an aerobic exercise intervention delivered with simultaneous cognitive training to inform future fully powered, large scale phase III RCTs.

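### The statement that investigators are blinded conflicts with their fidelity duties, and people exposed to allocation may settle outcome scores with the assessors

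*Protocol article*

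**What the plan says.** **Blinding safeguards.** Under Primary and secondary outcomes, the data collectors are blinded to allocation and to earlier data. Under Data collection, they are independent of the interventionists and meet participants only to collect data. The Discussion adds measures against unblinding. One is that "assessors will not interact with other staff who are not blinded", with exercise interventionists named as the staff meant, and that assessors hold separate meetings. Another is that "investigators will be blinded to group assignments".

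**Investigators' duties.** Treatment fidelity states that "monthly fidelity checks will be performed (total 3% of intervention sessions) by the investigators". The investigators also review 3% of exercise logs and, together with the coordinator, oversee study outcomes and intervention compliance, which includes time in the target intensity range and exercise dose. Under Safety, retention, adherence, and validation, interventionists may consult the investigators at once when needed and at weekly meetings.

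**Coordinator's duties.** Under Study preparation and randomization, "The study coordinator will log into the REDCap randomization module and enter a participant’s name/age"; the module is then to "record the assignment in a database that is only accessible to unblinded staff". Under Data entry, coding, and storage, the coordinator holds the link between names and IDs (shared only with interventionists involved in screening), reviews forms before entry and verifies REDCap. That section adds: "Data audits of electronic outcome data will be conducted by the study coordinator".

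**Scoring discrepancies.** If the person who collected a score and the person who entered it disagree, "a meeting with the investigators or study coordinator and involved study staff will be undertaken to ensure the correct data is in REDCap".

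**The concern.** Participants know which activity they do, so the single-blind label rests on the people who measure and handle the outcomes. The article gives readers two assurances about those people: investigators do not know the arm, and assessors have no dealings with staff who do. The duties listed elsewhere undercut the first assurance directly. They put the second in doubt, because the only people named to lead a score-discrepancy meeting are the investigators or the coordinator.

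Two things are at stake. The blinding description will be carried into the trial report, where a claim of investigator blinding would be inaccurate. And a person exposed to allocation could, knowingly or not, influence which of two conflicting values is kept. The outcome most open to this is the shuttle walk test (SWT), where laps are counted by staff. It carries Hypothesis 2a on aerobic fitness, and the Abstract counts aerobic fitness among the primary outcomes, although the outcomes section calls it secondary.

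**Working it through.** No stated figure has to be reproduced. The check sets promises beside duties; the arithmetic only gives a sense of exposure.

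**1. Can the investigators be blinded?** The arms are cycling while playing a game on screen, cycling alone, and stretching. Checking a session shows which is under way. Logs also separate the arms in part: cycling is set at 50–70% of heart rate reserve, stretching at 30% or less. Reviewing exercise dose and advising interventionists adds further exposure. The Discussion's statement is therefore incompatible with Treatment fidelity and with the Safety section.

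**2. Is the coordinator blinded?** The coordinator enters the participant into the module that makes the assignment, and the assignment record is open only to unblinded staff. The coordinator also oversees intervention compliance. Knowledge of allocation is the natural reading. It remains an inference, since no sentence gives the coordinator's blinding status.

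**3. Where does this reach the outcomes?** The discrepancy meeting brings the investigators or the coordinator together with the staff involved, who include whoever collected the score. If the investigators lead it, people shown in step 1 to be exposed meet an assessor about an outcome value. If the coordinator leads it, someone very likely unblinded does. Neither sits comfortably with separate meetings for assessors.

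**4. How many sessions are checked?** Inputs: 96 participants (Design); 36 sessions each and up to three participants per supervised visit (Delivery of the assigned activity); 3% checked (Treatment fidelity). Full attendance is assumed.

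- Participant-sessions: 96 × 36 = 3,456; 3% is 103.7, about 104.
- If every visit held three participants: 3,456 / 3 = 1,152 visits; 3% is 34.6, about 35 visits.

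**5. How many participants would that touch?** The article does not say how sessions are chosen. Assuming random, independent selection of 3% of participant-sessions:

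- At least one checked session: 1 − 0.97^36 = 0.67, or about 64 of 96 participants.
- At least one check or log review, if the logs are a separate 3% sample: 1 − 0.97^72 = 0.89.
- If all visits held three participants and each check covered only one of them, the rate per participant-session would be 1%: 1 − 0.99^36 = 0.30, or about 29 of 96.

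These figures describe exposure of investigators to allocation. They do not measure bias.

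**6. Which outcomes are open to it?** Cognitive scores come from the iPad-based NIH Toolbox and are exported, which leaves little to decide by hand. The recorded SWT lap count is a hand-collected value that a later meeting could change.

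**The case against.** The strongest reply is that the blinding that protects the outcomes is that of the assessors, and nothing in the article says a data collector learns an arm. A reader might infer that single-blinding has failed, or that every correction of an outcome passes through someone who knows the arm. The documents do not support either. Collectors stay separated from interventionists and from participants outside testing, they upload the Toolbox data themselves, and missing items go back to a collector. The discrepancy meeting may be no more than matching an entry to its source. This part of the reply stands and limits the point to a risk.

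Other limits also stand:

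- A reader might think SWT stopping decisions are exposed. They are made during the walk by a blinded collector, and no later audit can alter them.
- The coordinator's unblinded status is not stated. The Discussion's gloss names only exercise interventionists, and a meeting led by the coordinator is permitted, not required.
- A fidelity check need not mean watching a session in person, so 104 should not be quoted as a count of observed sessions.

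It can also be said that separation of duties belongs in the Study Manual of Operations, which is not shown. That would answer a complaint about missing detail. It does not answer a contradiction: the article itself states that investigators are blinded and also gives them duties that reveal the arm.

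**Conclusion.** The point holds in limited form. The contradiction over investigator blinding is firm: it follows from the article's own text and rests on no numerical assumption. The coordinator's knowledge of allocation is a strong inference. The route by which either could influence outcome scores is real but permissive, since it depends on discrepancies arising and on who attends the meeting.

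The investigators' fidelity checks cover up to about 104 participant-sessions at full attendance, or about 35 visits if all visits held three people. Under random selection roughly 30% to 67% of participants would have at least one check. The consequence is a route to detection bias, mainly for the SWT lap count and much less for the Toolbox scores. Loss of assessor blinding is not shown, and the documents give no basis for computing the size of any bias. The text should be corrected and the duties separated; nothing here invalidates the design.

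**What to change.** 1. Correct the Discussion. State that the coordinator, and any investigator who does fidelity checks, reviews logs or advises interventionists, are not blinded to allocation.
2. Bar those people from deciding outcome-score discrepancies. Have each one resolved against the source form or the iPad export by an existing blinded team member without allocation access. A data collector who is not assessing that participant would serve, and this choice also respects the rule that a participant's assessor does not see earlier data. The statistician is not a suitable choice, having created the randomisation schedule. Log each decision, with its reason, before unblinding.
3. Limit the coordinator's review of outcome data to completeness, with no meetings with assessors about scores.

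The cost is an edit to the protocol and the Manual of Operations and a small reshuffling of existing duties. It assumes at least two data collectors; the article uses the plural but gives no number.

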#### Statistical analyses

All variables will be summarized using appropriate descriptive statistics (e.g., means/standard deviation [SD] for continuous measures, and frequencies for categorical variables). Distributions will be visually inspected for outliers, and determine the best link and distribution combination for each outcome using the quasi information criteria [53]. Statistical assumptions will be checked. Baseline variables will be compared among the 3 groups to determine systematic differences using Pearson’s chi-square test (categorical variables) and one-way analysis of variance (ANOVA) or Kruskal-Wallis (continuous variables), as appropriate. Analysis will be accomplished using Statistical Product and Service Solutions (SPSS) for Windows or Statistical Analysis System (SAS). Variables that differ significantly among groups will be included as covariates in the models described below. All analyses will follow the intention-to-treat principle.
Aim 1: Determine the efficacy of the exergame in older adults with SCD. To test our hypothesis that exergame will improve global cognition more than cycling only and attention control, the ANOVA will be performed. If statistically significant results are identified, then we will perform post hoc analysis to determine how the changes in cognition differ between groups. If homogeneity of variances are supported across the three groups, we will conduct Tukey’s honestly significant different post hoc test. If homogeneity of variances are violated, then we will perform the Games Howell post hoc test. If significant covariates are identified, then analysis of covariance (ANCOVA) will be used instead. Linear simple and multiple regressions will be performed to assess association between the effects of exergames on global cognition and aerobic fitness. A *p* value < 0.05 will be used to determine statistical significance. Effect size (EF) calculated as EF = (mean exergames group − mean stretching group)/SD (stretching group) will be used to assess the clinical significance of the effects of exergames on cognitive and aerobic fitness outcomes listed above.Aim 2: Assess the distraction effect of exergame on aerobic fitness. Our hypothesis that exergame participants will achieve similar gains in aerobic fitness to cycling participants will be analyzed similarly to aim 1 hypothesis using ANOVA and post hoc test. In addition, heart rate monitor data will be utilized to compute intensity dose, to compare objective effort given during exergame and cycling only sessions. We hypothesize that the average %HRR achieved by exergame participants will not be significantly different compared to cycling only participants. A standard formula will be used to quantify the intensity dose and is as follows. Percent HRR (%HRR) averaged in each session will be calculated from the following variables (EHR = exercise session average heart rate, PHR = peak heart rate from SWT, and RHR = resting heart rate from SWT) and formula: %HRR = [(EHR − RHR)]/(PHR − RHR)]. The %HRR will be averaged across all sessions to give a quantifiable index of intensity to be used as a surrogate measure of distraction. Differences between exergames and cycling only groups on average %HRR will be assessed by independent *T* test.

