## Methods

### Design

The RCT will use a single-blind, 3-parallel group design, guided by CONSORT [31] and SPIRIT [32] guidelines (*n* = 96). We will use a 2:1:1 allocation ratio to randomize 48 subjects to exergame, 24 to cycling only, and 24 to attention control within age strata (< 75 and ≥ 75 years) and using permuted blocks of 4 and 8 participants. Based on our previous studies, we anticipate screening approximately 288 individuals to enroll 96 participants. Cognition and aerobic fitness will be assessed at baseline and 3 months. This study was approved by the university Institutional Review Board and registered at ClinicalTrials.gov on 17 March 2020 (study identifier NCT04311736).

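### Covariates are chosen by baseline significance tests, so the outcome's baseline score and the age stratum are almost always left out; this costs precision and leaves the model open, but does not inflate type I error

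*Protocol article*

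**What the plan says.** All references are to the protocol article.

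- **Baseline tests** (Statistical analyses): "Baseline variables will be compared among the 3 groups to determine systematic differences using Pearson’s chi-square test", with one-way ANOVA or Kruskal-Wallis for continuous variables.
- **Selection rule** (same section): "Variables that differ significantly among groups will be included as covariates in the models described below".
- **Default model** (Aim 1): to test the hypothesis that "exergame will improve global cognition more than cycling only and attention control, the ANOVA will be performed". The alternative is conditional: "If significant covariates are identified, then analysis of covariance (ANCOVA) will be used instead". Aim 2 analyses aerobic fitness in the same way and compares average %HRR by t test.
- **Form of the outcome**: the dependent variable of the ANOVA is never stated. The nearest hint is the follow-up step, where "we will perform post hoc analysis to determine how the changes in cognition differ between groups".
- **Model search** (Statistical analyses): distributions are inspected to "determine the best link and distribution combination for each outcome using the quasi information criteria".
- **Randomisation** (Design): allocation is 2:1:1 "within age strata (< 75 and ≥ 75 years) and using permuted blocks of 4 and 8 participants". The Discussion describes age as strongly related to cognition and adds that "we will stratify enrollment by age to equalize age distribution across groups".

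No section names the baseline value of the outcome or the age stratum as a fixed covariate.

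**The concern.** After proper randomisation, any baseline difference between arms is due to chance. A significance test of that difference says nothing about whether the variable predicts the outcome, and prediction is what makes a covariate worth having. The rule therefore discards the two covariates with the best claim to a place: the baseline measurement of the outcome, and the factor on which randomisation was stratified. It works against the stratification in particular, because the better the blocks balance age, the less likely age is to be selected.

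Two things are at stake. One is precision, in a trial of about 84 completers that the Discussion says should supply precise effect-size estimates for phase III. The other is that the model cannot be written down until the baseline data have been tested. The link and distribution search leaves the model open in a second way and does not fit with the named ANOVA, ANCOVA, Tukey and Games-Howell procedures.

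**Working it through.** **Inputs.** Arms of 48/24/24 (Design); 12% attrition, 80% power and effect size 0.85 (Sample size and power); p < 0.05 (Aim 1), taken as two-sided; test-retest reliability 0.90 for the composite (Global cognition), which is only a proxy for the correlation over 3 months. Assumed: r from 0.5 to 0.9, SD 1 at both visits, equal variances.

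**1. The plan's own figure.** Completers: 48 × 0.88 ≈ 42, 24 × 0.88 ≈ 21, so 42 + 21 + 21 = 84. The SE of exergame minus control without covariates is √(1/42 + 1/21) = 0.267 SD. Under the planned Tukey test (3 groups, 81 df, critical t 2.388), power at 0.85 SD is 78.4%, close to the stated 80%. With no multiplicity control it is 87.9%. The stated figure thus takes no credit for covariates and does not depend on this point.

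**2. How often the rule selects the key covariates.**
- *Baseline score*: a 5% test under randomisation passes about 5% of the time (4.7% to 5.1% in simulation), so the score is left out about 95% of the time.
- *Age stratum*: every complete block of 4 or 8 is exactly 2:1:1, so only unfinished blocks leave imbalance. In 12,000 simulated randomisations of 96 (share aged ≥ 75 assumed to be 20%, 35% or 50%), chi-square never reached p < 0.05; the smallest p was 0.57. Continuous age could still enter by chance.
- *Any covariate*: with k independent variables tested, the chance is 1 − 0.95^k, which is 40% for k = 10, 54% for k = 15 and 64% for k = 20. The protocol does not give k. Independence is a simplification, since the composite is built from the other cognitive tests.

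**3. Precision by formula.** Residual variance is 1 for the raw 3-month score, 2(1 − r) for change and 1 − r² for ANCOVA.

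| r | raw / ANCOVA | change / ANCOVA |
|---|---|---|
| 0.5 | 1/0.75 = 1.33 | 1.00/0.75 = 1.33 |
| 0.7 | 1/0.51 = 1.96 | 0.60/0.51 = 1.18 |
| 0.9 | 1/0.19 = 5.26 | 0.20/0.19 = 1.05 |

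These are variance ratios with no covariate ever entering.

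**4. Precision under the rule.** Simulated SE of exergame minus control, 42/21/21, with the baseline score entering when its test is significant:

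| r | change, rule v fixed ANCOVA | raw 3-month, rule v fixed ANCOVA |
|---|---|---|
| 0.5 | 0.260 v 0.231 (ratio 1.13) | 0.263 v 0.233 (1.13) |
| 0.7 | 0.204 v 0.192 (1.06) | 0.250 v 0.191 (1.31) |
| 0.9 | 0.118 v 0.116 (1.02) | 0.243 v 0.116 (2.09) |

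The columns come from separate runs of 4,000 or more replicates. A second run for change at r = 0.5 gives 0.260/0.233 = 1.12. For a 0.5 SD effect at r = 0.7 (two-sided 5%), power is 47% with the rule on raw scores, 68% with the rule on change and 74% with fixed ANCOVA.

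**5. Type I error.** With the rule on change scores it is 4.4% to 5.1%, against 4.6% to 5.2% for fixed ANCOVA. With the rule on raw scores it is 4.5%, 3.6% and 3.1% at r = 0.5, 0.7 and 0.9; other runs at r = 0.9 gave 2.3% to 2.9%. Omitting the stratum gives 3.7% or 2.5% if its correlation with the analysed outcome is 0.3 or 0.5 (assumed), against 4.7% or 5.3% with it included. Every departure of note is on the conservative side.

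**The case against.** The strongest reply is that the protocol probably means change scores. The follow-up step speaks of changes in cognition, and the hypotheses speak of improvement and of gains in fitness. The baseline is then already inside the outcome, and if the 3-month correlation is near the quoted reliability of 0.90, the loss is about 2% in SE. This largely stands. It limits the size of the problem but does not justify the rule: the outcome form is not stated, and over 3 months the correlation may fall below short-term reliability, which brings the loss towards 12%.

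A reader might infer that the standard error doubles. That needs both raw 3-month scores and r near 0.9, and the wording does not favour raw scores. A reader might also infer that choosing covariates after testing inflates false positives; the simulations show no inflation under either reading. Nor is the stated power undermined, since it assumes no covariate gain.

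The cost of omitting the age stratum cannot be fixed from the document. The Discussion links age to cognition, not to 3-month change, so on change scores that cost may be small.

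Finally, covariate detail is often left to a statistical analysis plan. Here, however, the protocol states a rule, and the rule is the problem.

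**Conclusion.** The point holds as a defect of efficiency and pre-specification, not of validity. The stated rule omits the baseline score about 95% of the time and the age stratum practically always. It also leaves a 40% to 64% chance that some covariate enters by accident, if 10 to 20 independent variables are tested. On the likelier change-score reading the SE is about 2% to 12% larger than necessary. On the raw-score reading it is about 12% to 110% larger, with a conservative test. These ranges rest on r between 0.5 and 0.9, equal variances and 42/21/21 completers. The link and distribution search is a separate inconsistency with the named ANOVA and adds to the uncertainty about the model. Severity: should fix.

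**What to change.** - Drop baseline significance tests as a way of selecting covariates, and keep the baseline comparison descriptive.
- For each cognitive and fitness outcome measured at baseline and 3 months, pre-specify an ANCOVA of the 3-month score on arm, the baseline value of that outcome and age stratum (< 75 / ≥ 75). This also settles the form of the outcome, and it applies whichever outcome is finally named as primary.
- Keep the planned pairwise multiplicity control and apply it to the adjusted means.
- For average %HRR, which has no baseline value, adjust for age stratum only.
- Remove the quasi-information search over links and distributions for these outcomes.

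The cost is wording in the protocol or analysis plan, plus the ethics submission that the Ethics section requires for amendments. Age and the baseline measures are already collected (Table 2), and the sample size is unchanged. The change should be made before anyone examines outcome data by arm.

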**Methods/design:**

The purpose of this single-blinded, 3-parallel group randomized controlled trial is to test the synergistic efficacy of an exergame intervention (simultaneous moderate-intensity aerobic cycling and cognitive training) on cognition and aerobic fitness in community-dwelling older adults with SCD. The Exergames Study will randomize 96 participants on a 2:1:1 allocation ratio to 3-month exergame, cycling only, or attention control (stretching). Primary outcomes include global cognition and aerobic fitness, which will be assessed at baseline and after 3 months. The specific aims of the Exergames Study are to (1) determine the efficacy of the exergame in older adults with SCD and (2) assess the distraction effect of exergame on aerobic fitness. Data will be analyzed using ANOVA following intention-to-treat.

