#### Sample size and power

Enrollment of 96 subjects with 12% attrition at 3 months will give us 80% power to detect a .85 effect size between exergame and attention control.

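### The ANOVA of change named in the plan needs a 3-month score, so what is labelled intention-to-treat is, as written, an available-case analysis of about 84 of 96 participants

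*Protocol article*

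**What the plan says.** The principle appears twice. The Abstract ties it to the test: "Data will be analyzed using ANOVA following intention-to-treat". The Statistical analyses section makes it general: "All analyses will follow the intention-to-treat principle".

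The same section names the test for Aim 1. To examine whether "exergame will improve global cognition more than cycling only and attention control, the ANOVA will be performed", and a significant result leads to "post hoc analysis to determine how the changes in cognition differ between groups". The compared quantity is therefore change. There is one alternative: "If significant covariates are identified, then analysis of covariance (ANCOVA) will be used instead". The Aim 2 comparison of aerobic fitness follows the same route.

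On timing, the Design section says "Cognition and aerobic fitness will be assessed at baseline and 3 months". On expected loss, the Sample size and power section starts from "Enrollment of 96 subjects with 12% attrition at 3 months".

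Under Data management, the article says that missing data will be sent back for collection, and that efforts will be made to obtain data from people who withdraw so that they can be analysed. It names no analysis set or statistical method for those who still have no 3-month score.

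**The concern.** The article fixes a principle, a test and an expected loss, and the three do not fit together. A change score from two visits does not exist without the second visit, and no intermediate outcome visit could stand in for it. The test therefore leaves out the people the power statement expects to lose, while the result would be reported as intention-to-treat.

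Loss need not be equal across arms. Two arms do moderate-intensity cycling, one of them with a simultaneous cognitive task, and the third does light stretching. If those lost from one arm differ from those who stay, for instance in baseline cognition, the observed change in that arm no longer represents everyone randomised to it. The Abstract and the Discussion both say the trial is meant to supply effect sizes for later trials, so a shifted contrast would carry forward into their planning.

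**Working it through.** **Inputs from the protocol article.** 96 randomised 2:1:1 as 48 exergame, 24 cycling and 24 attention control (Design); outcomes at baseline and 3 months (Design); 12% attrition, 80% power and effect size 0.85 for exergame against control (Sample size and power); significance at 0.05 and Tukey as the post hoc test when variances are homogeneous (Statistical analyses). The alpha behind the power statement is not given.

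**Step 1: who can enter the test.** An ANOVA of change, an ANCOVA with added covariates, and a classical repeated-measures ANOVA on two visits all need the 3-month value. Switching to ANCOVA when baseline variables differ does not bring anyone back.

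**Step 2: how many.** Lost: 96 × 0.12 = 11.5. Left: 96 × 0.88 = 84.5. By arm, at equal loss: 48 × 0.88 = 42.2 and 24 × 0.88 = 21.1 in each smaller arm. In whole numbers that is 42 + 21 + 21 = 84. This takes the 12% as the share still without a score after retrieval.

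**Step 3: the plan's own power figure.** I used the noncentral t distribution with noncentrality 0.85 / √(1/n₁ + 1/n₂). For 42 and 21 the standard error is √(1/42 + 1/21) = 0.267 SD, and the noncentrality is 0.85 / 0.267 = 3.18.

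| Exergame vs control, effect 0.85 | 42 vs 21 | 48 vs 24 |
|---|---|---|
| two-sided 0.05 | 87.9% | 91.8% |
| two-sided 0.025 | 80.9% | 86.4% |
| two-sided 0.0167 | 76.2% | 82.5% |
| Tukey, three groups | 78.4% | 84.4% |

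The stated 80% is matched within 2 points by 42 vs 21, at 0.025 or with Tukey. The detectable effect for 42 vs 21 at 0.025 is 0.84, close to 0.85. This fits a test to which the lost 12% contribute nothing. It is corroboration only, because the alpha is unstated and other combinations also come close.

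**Step 4: what bias could look like (assumptions, not in the documents).** Let p be the share lost in an arm, and s the amount by which the lost would have changed less than those observed, in SD. The mean for everyone in the arm is the observed mean minus p × s. The observed exergame-control contrast therefore exceeds the all-randomised contrast by p_E × s_E − p_C × s_C, which is s × (p_E − p_C) when s is common to both arms.

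| Loss: exergame / cycling / control | Overall loss | s = 0.5 | s = 1.0 |
|---|---|---|---|
| 16% / 12% / 4% | (7.68 + 2.88 + 0.96)/96 = 12% | +0.06 | +0.12 |
| 12% / 12% / 12% | 12% | 0 | 0 |
| 8% / 12% / 20% | (3.84 + 2.88 + 4.80)/96 = 12% | −0.06 | −0.12 |

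Equal loss does not protect if the shortfalls differ. At 12% in both arms, a difference in shortfall of 0.25, 0.5 or 1.0 SD shifts the contrast by 0.03, 0.06 or 0.12 SD.

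**Step 5: scale.** 0.06 / 0.85 = 7% and 0.12 / 0.85 = 14% of the design effect. Against the standard error, 0.06 / 0.267 = 0.22 and 0.12 / 0.267 = 0.45.

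**The case against.** The strongest reply is that this is an omission, not an error. Analysis sets and missing-data methods commonly sit in a full protocol or analysis plan, neither of which is shown. Nothing in the article says that people without a 3-month score are excluded, and nothing rules out imputation before the ANOVA. The section also mentions choosing a link and distribution for each outcome, so the model form is not wholly settled. Some would add that intention-to-treat means analysis by assigned arm with full effort at follow-up, which the article does provide.

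Much of this stands. Silence on missing data alone would be no finding, and an unseen plan may already resolve the matter. The 12% is a planning allowance already taken off the sample, so power is protected. What survives is narrower: the article is specific down to the choice of post hoc test, and the test it names, run as written, cannot include every randomised participant.

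A reader might go further and infer that the trial will report a completer analysis. The text does not support that. People who stop or withdraw are to be followed up and included, so only those whose score cannot be retrieved drop out. Nor does the article call the Aim 1 test one-way: that word is attached only to baseline comparisons, "one-way analysis of variance (ANOVA) or Kruskal-Wallis (continuous variables), as appropriate".

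The proposed model also has limits. With two visits, a participant with only a baseline score adds little information on the treatment contrast, and the model assumes missing at random. It does not correct loss that depends on the unseen 3-month result.

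**Conclusion.** The point holds in a limited form. The article promises intention-to-treat, while the change-score ANOVA it names is an available-case analysis of about 84 of 96 participants. That count rests on the 12% planning figure remaining after retrieval. The analysis can be biased if loss differs by arm and depends on baseline score.

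It would be wrong to infer that the exergame effect will be overstated. The documents give neither arm-specific loss nor any difference between those lost and those observed. The illustrative shift of 0.06 to 0.12 SD can favour either arm and vanishes when loss and shortfall are both equal. Arm-level loss would also be coarse: 4% of 24 is about one person. A shift of that size is less than half a standard error of the contrast, so it is modest for the test but relevant to the effect-size estimates the trial is meant to provide. The comparison of average %HRR under Aim 2 uses session data and does not depend on a 3-month score.

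**What to change.** For cognition and aerobic fitness, make the primary analysis a constrained longitudinal model: baseline and 3-month scores both as outcomes, a common baseline mean across arms, age stratum as covariate, and every randomised participant included as assigned. This remains valid when loss depends on baseline score and arm. An acceptable alternative is ANCOVA on baseline score and age stratum after multiple imputation by arm, using session attendance and the monthly activity and medical-change data.

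Because either analysis assumes missing at random, add a delta-adjusted sensitivity analysis that shifts the unobserved 3-month scores over a stated range, by arm and in both directions. Report any ANOVA of observed change as available-case, with the number analysed and the number lost in each arm. If the full protocol or analysis plan already names the analysis set and missing-data method, bring the article's wording into line with it.

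The cost is plan wording and modest programming. The attendance and monthly data are already being collected, and no extra visits are needed.
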